## Abstract

**Introduction:**

A subgroup of adolescents and young adults diagnosed with cancer during adolescence reports elevated levels of anxiety and depressive symptoms and unmet needs for psychological support. Evidence-based psychological treatments tailored for this population are lacking. This protocol describes a feasibility study of a guided-internet-administered self-help programme (YoungCan) primarily targeting symptoms of anxiety and depression among young persons diagnosed with cancer during adolescence and of the planned study procedures for a future controlled trial.

**Methods/analysis:**

The study is an uncontrolled feasibility trial with a pre-post and 3-month follow-up design. Potential participants aged 15–25 years, diagnosed with cancer during adolescence, will be identified via the Swedish Childhood Cancer Registry. 30 participants will be included. Participants will receive YoungCan, a 12-week therapist-guided, internet-administered self-help programme consisting primarily of cognitive–behavioural therapy organised into individually assigned modules targeting depressive symptoms, worry and anxiety, body dissatisfaction and post-traumatic stress. Interactive peer support and psychoeducative functions are also available. Feasibility outcomes include: recruitment and eligibility criteria; data collection; attrition; resources needed to complete the study and programme; safety procedures; participants' and therapists' adherence to the programme; and participants' acceptability of the programme and study methodology. Additionally, mechanisms of impact will be explored and data regarding symptoms of anxiety, depression, post-traumatic stress, body dissatisfaction, reactions to social interactions, quality of life, axis I diagnoses according to the Mini International Neuropsychiatric Interview and healthcare service use will be collected. Exploratory analyses of changes in targeted outcomes will be conducted.

**Ethics/dissemination:**

This feasibility protocol was approved by the Regional Ethical Review Board in Uppsala, Sweden (ref: 2016/210). Findings will be disseminated to relevant research, clinical, health service and patient communities through publications in peer-reviewed and popular science journals and presentations at scientific and clinical conferences.

**Trial registration number:**

ISRCTN97835363.

Strengths and limitations of this studyThis study will examine the feasibility and acceptability of a guided internet-administered self-help programme and of the planned procedures to evaluate it using qualitative and quantitative methods.The main challenges related to the programme and study procedures will be identified and findings will be used to refine the programme and design a controlled trial.Development of the guided self-help programme has included extensive involvement and consulting of theoretical, clinical and end-user expertise to ensure its scientific and clinical relevance.The main study limitations include the uncontrolled design, the relatively short follow-up and the lack of power to examine efficacy.

## Introduction

During the past decade, adolescents diagnosed with cancer have received increased attention due to the specific challenges experienced in managing the short-term and long-term stressors associated with cancer and its treatment while at the same time transitioning from childhood to adulthood.^1^
^2^ Adolescence and emerging adulthood^3^ are characterised by rapid physical, social and psychological changes and include developmental challenges related to independence, relationships, education and identity. These challenges are often demanding in themselves and can be further complicated by the cancer experience.^1^ Given the transitions experienced during adolescence and emerging adulthood, it has been hypothesised that people diagnosed with cancer during adolescence may have increased vulnerability to symptoms of anxiety, depression and post-traumatic stress. Indeed, some studies have shown that, compared to community controls^4^
^5^ and people diagnosed at a younger age,^6^
^7^ people diagnosed with cancer during adolescence report a lower level of health-related quality of life and a higher level of psychological distress, while others have not found such differences^8^ or have even found lower levels of psychological distress compared to population norms^9^ and controls.^10^ However, across the majority of studies, a subgroup of adolescent and young adult survivors of cancer during adolescence report symptoms of anxiety and/or depression at a clinically relevant level. Importantly, longitudinal studies show that the development of cancer-related symptoms is nonlinear, with people reporting symptoms of anxiety and depression years after the completion of treatment.^11^
^12^

Studies examining the psychological needs experienced by survivors of adolescent cancer are scarce and those few which have been carried out indicate that the existing needs are often unmet.^13^
^14^ Access to mental health services and social support, including peer-to-peer interaction, are some of the most common unmet needs reported by adolescents and young adults with cancer.^15^ Despite the unique challenges and needs of adolescents and young adults, age-appropriate psychosocial interventions are lacking.^16–18^

Given the reports of elevated levels of psychological distress after completion of treatment for cancer during adolescence^5–7^and the lack of evidence-based psychological interventions,^16–18^ coupled with difficulties in accessing psychological support services,^13–15^ there is a need to increase access to psychological support after adolescent cancer.^4^
^15^ Evidence is accumulating that internet-based cognitive–behavioural therapy (ICBT) is effective both clinically and in terms of cost for treatment of depression and anxiety symptomatology in adults^19^ and young people^20^ with effects equivalent to face-to-face CBT.^19^
^21^ ICBT programmes typically include provision of self-help material via the internet^22^ but differ with regard to the type and nature of support provided to engage the patient with the self-help material, ranging from self-administered (no specific support) to therapist-guided (provision of initial support session providing a rationale and regular scheduled support sessions in which progress and process issues are discussed).^23^
^24^

The important advantages of ICBT are that it can be delivered at a time and place convenient to the individual and reach people in remote locations^25^
^26^ and thereby increase access to evidence-based treatments. However, most of the existing ICBT programmes are developed for mental health populations, and smaller effect sizes have been shown for people with physical health conditions than for mental health populations.^27^ Taken together, there is a need for psychological interventions addressing the diverse manifestations of illness-related distress and challenges faced by somatic populations.^28^
^29^ For example, survivors of adolescent cancer struggle with difficulties related to parental overprotectiveness,^30^ loneliness and isolation,^31–33^ social interaction,^34^ school difficulties and lagging behind,^31^
^33^ worry related to potential infertility,^34^ health anxiety and fear of recurrence,^31^
^34^
^35^ changes in body appearance and self-image,^31^
^36^
^37^ and existential thoughts related to losses and threat to life.^34^
^38^ It may be important to address these difficulties when developing psychological interventions for young people diagnosed with cancer during adolescence in order to improve acceptability, engagement and effectiveness.

Although internet-based psychological self-help may suit the needs of young cancer survivors, only two published studies have investigated the feasibility and preliminary clinical efficacy of ICBT for young people diagnosed with cancer during childhood or adolescence.^39–41^ One study investigated the feasibility of an online CBT group intervention to prevent psychosocial problems among adolescents who had completed treatment for cancer diagnosed during childhood and found high levels of satisfaction with the intervention among both participants and the psychologists administering the intervention.^39^ Another study examined the feasibility and preliminary efficacy of an ICBT programme to reduce symptoms of post-traumatic stress and anxiety among adolescent and young adult survivors of cancer during childhood and found the intervention to be acceptable and efficacious with pre-post medium effect sizes on post-traumatic stress and anxiety which were sustained at 3-month follow-up.^40^
^41^ However, to the best of our knowledge, no study has evaluated guided ICBT specifically developed to reduce symptoms of anxiety and depression among adolescents and young adults diagnosed with cancer during adolescence who have completed cancer treatment.

The primary aim of the planned study is to investigate the feasibility of a guided internet-administered self-help programme (YoungCan) primarily targeting symptoms of anxiety and depression among young people diagnosed with cancer during adolescence, and of the planned study procedures for a future controlled trial to evaluate the programme's clinical efficacy and cost-effectiveness. The feasibility outcomes concern methodological, procedural and clinical uncertainties,^42–44^ and exploratory analyses of changes in targeted outcomes from baseline to postbaseline assessments will be conducted.

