### Eligibility criteria

Eligible participants will be aged 15–25 years at study start; have been diagnosed with cancer when aged 13–18 years; have been treated at a paediatric oncology unit in Gothenburg, Lund, Linköping or Umeå in Sweden; have completed successful cancer treatment (according to the paediatric oncology unit if the person is 15–17 years at study start or according to self-report if the person is ≥18 years at study start); be able to read and write text in Swedish; have access to email, the internet and a mobile telephone, and report a need for psychological support. Little data are available to guide the selection of screening measures for this population.^47^
^48^ As such, no cut-off scores on screening measures will be used to determine inclusion into the study; however, the feasibility of screening procedures will be examined to inform the procedures for a future controlled trial.

Potential participants will be excluded if they currently receive psychotherapy or if they display symptoms of severe depression, active suicidality, psychosis, bipolar disorder and/or alcohol and/or substance abuse in immediate need of treatment (based on a clinical assessment combining information from the 9-item Patient Health Questionnaire (PHQ-9)^49^ and the Mini-International Neuropsychiatric Interview (MINI.)^50^). People excluded on this basis will be guided to appropriate healthcare.

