### Informed consent and eligibility interview

People who have been contacted via telephone or post and who are interested in participating will be directed to a secure website where they can register, provide informed consent and answer questions regarding symptoms of depression (PHQ-9^49^) and Generalized Anxiety Disorder 7-item scale (GAD-7^57^). Written information about the study will be sent to caregivers of people aged 15–17 years who have registered on the website.

Potential participants will thereafter be contacted via telephone by a clinical psychologist for an eligibility interview to confirm inclusion criteria, that is, completed successful cancer treatment; able to read and write text in Swedish; have access to email, the internet and a mobile telephone; and not currently receiving psychotherapy. The psychologist will also provide a description of the programme, its aims and the types of problems addressed. Potential participants will be asked about their own situation and whether they experience any of the problems addressed in the programme. They will thereafter decide themselves whether they have a need for the support provided, with young adults considered experts of their own perceived needs. Potential participants meeting the inclusion criteria and perceiving a need for psychological support will be interviewed with the MINI^50^ to identify people with psychiatric problems in need of immediate treatment or further examination. People reporting such problems are excluded and guided to appropriate healthcare services. If a potential participant reports suicide ideation but the risk of suicide is assessed as low, the person is offered participation and a safety plan is set up collaboratively. People meeting the eligibility criteria will be offered the opportunity to participate. If the person is aged 15–17 years, an assessment of whether he/she understands what participation implies will be performed to determine whether his/her consent to participate is sufficient or if it needs to be complemented with caregiver consent. If the person appears not to understand the implication of participation, he/she will be asked for permission for study personnel to collect informed consent from his/her caregiver(s). If the caregiver(s) does(do) not consent, participation will not be continued. The flow of participants through the study is shown in figure 1.

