#### Psychological and health economics outcomes

The feasibility of using a number of psychological and health economics measurements will be examined to assess whether or not to include them in a controlled study. The PHQ-9^49^ will be used to measure symptoms of depression and the GAD-7^57^ to measure anxiety symptoms. Body dissatisfaction will be measured with the Body Image Scale (BIS)^71^ and post-traumatic stress symptoms using the Posttraumatic Stress Disorder Checklist—Civilian version (PCL-C).^72^ Reactions to social interaction situations will be measured with the Social Interaction Anxiety Scale (SIAS).^73^ The EuroQol EQ-5D^74^ will be used to calculate quality-adjusted life years. Aspects regarding use of healthcare services, employment, absence and sick leave will be examined with a modified short version of the Trimbos and Institute of Medical Technology Assessment Cost Questionnaire for Psychiatry (TiC-P),^75^ assessing direct and indirect medical costs and indirect non-medical costs.

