### Data collection

Psychological and health economics-related self-reported data will be collected at the eligibility interview, the baseline assessment and the assessments 3 and 6 months after the baseline assessment. Data will be collected either via telephone or online via the Portal. Prompts will be sent via text message and reminders will be sent via text message or provided by telephone. The outcome measures and mode of administration, at each assessment, are shown in table 2.

**Table 2 BMJOPEN2016013906TB2:** Outcome measures at each assessment

Measure	Eligibility interview	Baseline assessment	Assessment at 3 months postbaseline	Assessment at 6 months postbaseline	Mode of administration
Demographics and clinical variables		x			Online
PHQ-9	x		x	x	Online
GAD-7	x		x	x	Online
BIS		x	x	x	Online
PCL-C		x	x	x	Online
SIAS		x	x	x	Online
EQ-5D		x	x	x	Online
Modified TiC-P		x	x	x	Online
MINI		x	x	x	Telephone

BIS, Body Image Scale; EQ-5D, EuroQol 5-dimension questionnaire; GAD-7, Generalized Anxiety Disorder 7-item scale; MINI, Mini-International Neuropsychiatric Interview; PHQ-9, 9-item Patient Health Questionnaire; PCL-C, Posttraumatic Stress Disorder Checklist-Civilian version; SIAS, Social Interaction Anxiety Scale; TiC-P, Trimbos and Institute of Medical Technology Assessment Cost Questionnaire for Psychiatry.

Data collection via telephone at 3 and 6 months post baseline will be performed by psychologists and clinical psychology students not otherwise involved in the study. Potential participants/participants who report psychiatric symptoms in need of treatment or further psychiatric examination will be guided to appropriate healthcare and if the person is aged 15–17 years, their caregiver(s) will be informed.

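### PHQ-9 and GAD-7 have no baseline measurement, so their change scores must start from the registration score, an unstated time before baseline

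*Protocol article*

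**What the plan says.** The Introduction describes a programme "primarily targeting symptoms of anxiety and depression among young people diagnosed with cancer during adolescence" and states that "exploratory analyses of changes in targeted outcomes from baseline to postbaseline assessments will be conducted". The section on psychological and health economics outcomes assigns the instruments: the PHQ-9 "will be used to measure symptoms of depression and the GAD-7^57^ to measure anxiety symptoms".

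Table 2 (Data collection) has separate columns for the eligibility interview, the baseline assessment, and the assessments 3 and 6 months after baseline. The PHQ-9 and GAD-7 rows ("PHQ-9 x x x Online" and "GAD-7 x x x Online") carry three marks each: eligibility, 3 months and 6 months. Their baseline cells are empty. The same section times both follow-ups from the baseline assessment.

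The section on informed consent and the eligibility interview says when the first scores are obtained. Interested people go to a website where they register, "provide informed consent and answer questions regarding symptoms of depression (PHQ-9^49^) and Generalized Anxiety Disorder 7-item scale (GAD-7^57". The psychologist's telephone eligibility interview comes after that. Under Eligibility criteria, exclusion for severe depression and other acute problems is "based on a clinical assessment combining information from the 9-item Patient Health Questionnaire" and the MINI.

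The Quantitative analyses section reports descriptive statistics and change scores at the eligibility interview, at baseline, and 3 and 6 months after baseline. It does not say which time point is the reference for change.

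**The concern.** The stated analysis and the schedule do not match for the two outcomes that matter most to the programme. A change from baseline needs a value at baseline, and none is collected for depression or anxiety. The only available starting value is the registration score.

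Three things follow:

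- The PHQ-9 and GAD-7 change scores cover a longer period than those of the other scales, by an amount that the protocol neither limits nor reports.
- Symptom change between registration and baseline is counted as pre-post change. With no control group, nothing separates it from change during the programme.
- The PHQ-9 score is both an input to the exclusion decision and the reference for change, so selection on a noisy measurement can enter the result.

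The study is meant to test procedures for a controlled trial, so the assessment schedule is itself part of what is being piloted.

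**Working it through.** No figure in the protocol can be reproduced here. The check is a reading of Table 2 against the text, followed by a decomposition of the change score.

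**Step 1: pre-treatment measurements in Table 2**

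| Instrument | Eligibility interview | Baseline | 3 months | 6 months |
|---|---|---|---|---|
| PHQ-9 | yes | blank | yes | yes |
| GAD-7 | yes | blank | yes | yes |
| BIS, PCL-C, SIAS, EQ-5D, TiC-P, MINI | blank | yes | yes | yes |

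Of 8 outcome instruments, 6 have a baseline value and 2 do not. Those 2 measure the main targets.

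**Step 2: is the blank a misread table?** Unlikely. The other six rows are consistently placed one column later. The consent section independently puts PHQ-9 and GAD-7 at registration, and no section repeats them at baseline.

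**Step 3: order of events.** Registration with PHQ-9 and GAD-7 comes first. The telephone eligibility interview follows, then the person's own decision about need, then the MINI. For some aged 15–17, caregiver consent comes next. Inclusion comes last. No duration is given for this sequence.

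**Step 4: intervals.** Let g be the time from registration to the baseline assessment.

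- Scales measured at baseline: change over 3 and 6 months.
- PHQ-9 and GAD-7: change over 3 + g and 6 + g months.

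**Step 5: what the change score contains.** Write R for the registration score, B for the score that would have been obtained at baseline, and F for the follow-up score. Then

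F − R = (F − B) + (B − R).

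The first bracket is the change that the Introduction describes. The second is pre-treatment drift plus any regression to the mean. Since B is never measured, the two cannot be separated.

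**Step 6: can the size of (B − R) be derived?** No. The protocol gives no SD, no retest reliability, no gap and no selection model. A simulation on assumed values shows how far the answer depends on the selection mechanism. The assumptions are PHQ-9 mean 7 and SD 5.5, retest reliability 0.6, 0.7 or 0.8, and no treatment effect. Wherever entry is modelled, its probability is logistic and centred at 10. Exclusion is at an assumed score of 20 or more. The table gives the mean fall from R to a repeat score, in points:

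| Assumed selection | Reliability 0.6 | 0.7 | 0.8 |
|---|---|---|---|
| Entry depends steeply on the observed score (logistic scale 2) | about 1.96 | about 1.47 | about 0.98 |
| Entry depends on true severity (logistic scale 2) | −0.16 | −0.12 | −0.09 |
| Only the exclusion acts | −0.05 | −0.04 | −0.03 |

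With a weaker dependence on the observed score (logistic scale 5), the fall is about 1.1 points at reliability 0.6 and 0.56 at 0.8. The result runs from about 2 points of spurious improvement to a slight spurious worsening. The protocol does not say which mechanism applies.

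**The case against.** **A change can still be calculated.** The registration score precedes treatment, and the Quantitative analyses section names the eligibility interview as a reporting point. This stands. A reader might infer that no pre-post change is available for these scales, and that would be wrong. What is missing is a change from baseline as the Introduction words it, and any statement that the registration score takes its place.

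**The gap may be short.** The consent section places the MINI within the eligibility procedure, while Table 2 marks its only pre-treatment administration at baseline. The Ethics section counts three assessments of participants' need for other services. Eligibility and baseline may therefore be nearly one block. This also stands as a possibility. No delay of any particular number of weeks can be read from the protocol, and the two accounts of the MINI need to be reconciled.

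**Regression to the mean is not established.** A reader might infer a sizeable artefactual improvement because people enter when distressed. The documents do not support that. People are found in a registry and telephoned in alphabetical order, they decide about their need after the score is taken, and no screening cut-off governs inclusion. Self-selection on perceived need could push one way and exclusion of severe depression the other. Scales taken at baseline are not necessarily free of selection effects either.

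**The stakes are limited.** Feasibility is primary, lack of power for efficacy is declared, and no criterion in Table 1 uses a PHQ-9 or GAD-7 change. This stands and sets the weight of the point. A reader might also infer that the controlled trial will inherit this schedule, but the protocol only says that the measures are being tried out for it.

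**A later analysis plan could clarify.** It could name the reference, but it could not supply a measurement that the schedule does not collect.

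**Conclusion.** The mismatch is real and rests on two independent places in the protocol: Table 2 and the consent section. PHQ-9 and GAD-7 have one pre-treatment value, taken at registration. Their change scores must start there, cover 3 + g or 6 + g months with g unstated, and include any change before treatment. For PHQ-9 the same value also informs exclusion.

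No bias in points can be attached to this. The simulated range reflects assumptions about selection, not facts about this study. Two assumptions remain: that Table 2 is the complete schedule, and that some time passes between registration and baseline. If the two are effectively simultaneous, what remains is a labelling fault.

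The point is modest. It should be corrected because it touches the programme's main targets and costs little, but it does not affect the feasibility conclusions or the progression criteria.

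**What to change.** Preferred:

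- Add PHQ-9 and GAD-7 to the baseline column of Table 2 and calculate change from that value.
- Keep the registration scores for the eligibility assessment.
- Report the registration-to-baseline interval, and the mean difference between the two scores with a 95% CI. This shows how much change occurs before treatment and would help in planning the controlled trial.

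The cost is 9 + 7 = 16 extra online items at an assessment that already includes five self-report instruments and the MINI, plus one table edit. A baseline value cannot be recovered once participants have started.

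Minimum, if the scales are not repeated: state in the Introduction and in Quantitative analyses that the registration score is the pre-treatment reference for these two scales, and report its interval to baseline. This costs only wording, but it leaves drift inside the change scores.

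In either case, reconcile the consent section and Table 2 on whether the pre-treatment MINI belongs to the eligibility procedure or to the baseline assessment.
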